### Data management

Study data is collected and managed using the Research Electronic Data Capture (REDCap™) tools hosted by the University of California Davis Health System Clinical and Translational Science Center [23]. REDCap is a secure, web-based application designed to support data capture for research studies, providing 1) an intuitive interface for validated data entry; 2) audit trails for tracking data manipulation and export procedures; 3) automated export procedures for seamless data downloads to common statistical packages; and 4) procedures for importing data from external sources.

Data quality is assured by several methods, including double data entry, electronic data checking, and laboratory-specific use of certified and non-certified controls and standards. Data that is collected in real-time during study visits is recorded in a master datasheet using MS Excel and directly entered into the REDCap™ database by the data manager. Using feature number 4 described above, the MS Excel sheet is periodically uploaded to the REDCap™ database, where inconsistencies between the manually entered data and the uploaded data are identified and flagged for investigation. As previously described, responses to questionnaires are entered directly into the database using the survey tool. Responses are downloaded from the REDCap™ database and entered into pre-programmed scoring sheets, which use the macros and conditional formatting capabilities of MS Excel. Surveys are scored according to published guidelines and scores are entered into the databases along with the original responses.

Statistical analysis of reliability and measurement error will be performed for assessment tools utilizing self-reporting methods, including the Profile of Mood States and Yale Food Addiction Scale questionnaires. Cronbach’s alpha will be calculated according to pre-defined dimensions for respective scales.

Biochemical data are generated according to assay manufacturer guidelines using certified controls whenever possible. Laboratory-specific use of standards and non-certified controls are recorded to evaluate data quality and maintain quality control.

### Anticipated results

Participant characteristics will be calculated as means and standard deviations, medians and percentiles, and percentages, overall and by phenotype, once determined. Differences in demographic variables and general characteristics across phenotypic groups will be tested using analysis of variance and logistic regression with multiple factors. Continuous variables will be mathematically transformed when data are not normally distributed, as needed. Non-parametric tests will be used for variables that do not meet assumptions for statistical tests after transformation attempts. Dietary quality scores will be calculated using standard methods including the Healthy Eating Index [24], which utilizes a density approach for specific intake per 1000 kcal or as a percent of caloric intake, or by cluster analysis of collected data. Recent and habitual macronutrient and micronutrient intake will be summarized from 24-h dietary recalls and food frequency questionnaires respectively and used in specific analyses. In the former, marked under- or over reporting will be identified using a ratio of energy intake: observed resting metabolic rate. In the latter, nutrient densities will be calculated and used in analyses.

Within each area of study, participants will be grouped using cluster analysis to create area-specific phenotypes. The four main areas of study are 1) Immunology and gut microbiota, 2) metabolomics, 3) dietary intake and physical activity, and 4) stress reactivity and cognitive function. Chi-square tests and loglinear models will be used to compare the defined phenotypes between areas of study.

Cluster analysis will be used to identify overall phenotypic groups within the study population. Component variables will be compared between clusters using analysis of variance. Sampling bins, overall phenotypic groups, and standard phenotypes will be compared using chi-square tests and loglinear models. Definitions of phenotypic groups from the literature will be applied to the current data set as “standard” phenotypic groups.

Metabolomics data will be used to calculate product: substrate ratios which will be explored as unique phenotypic descriptors [25]. Multi-omic analyses will employ partial correlations to estimate latent data networks [26]. Analysis-specific statistical plans will be published at a later date.

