**Discussion:**

This study will provide novel insights into metabolic variability among healthy adults in balanced strata defined by sex, age and body mass index. Usual dietary intake and physical activity will be evaluated across these strata to determine how diet is associated with health status defined using many indicators including immune function, metabolism, body composition, physiology, response to exercise andmeal challenges and neuroendocrine assessment. A principal study goal is to identify dietary and other personal factors that will differentiate different levels of "health" among study participants.

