## Statistical analysis

### Sample size calculations

The sample size calculation is designed to detect a potentially small correlation between dietary variables and our primary outcomes, i.e. systemic immune activation and metabolomics responses to a mixed macronutrient challenge meal. In order to explain approximately 3% of the variation in inflammation, we need to detect a correlation coefficient (R) = 0.18 (R^2^ = 0.032 ≈ 3%). Establishing 95% power and α = 0.05 level of significance, the target sample size is 22 in each of the 18 categories defined by age, sex, and BMI. In addition, we aim to enroll an additional 10% of the calculated sample size to account for attrition.

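### ANOVA of the clustering variables across the clusters they formed gives invalid p-values; that comparison should be descriptive only

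*Protocol article*

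**What the plan says.** Under Statistical analysis, Anticipated results, the article plans clustering at two levels. The first is by area: "Within each area of study, participants will be grouped using cluster analysis to create area-specific phenotypes". The second is across the whole study: "Cluster analysis will be used to identify overall phenotypic groups within the study population". The sentence directly after the second is "Component variables will be compared between clusters using analysis of variance", and the next is "Sampling bins, overall phenotypic groups, and standard phenotypes will be compared using chi-square tests and loglinear models".

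Earlier in the same section, a separate sentence plans tests of demographic variables and general characteristics across the phenotypic groups. The section ends by deferring analysis-specific plans to later publication. It does not list the inputs to the overall clusters, and it does not describe the ANOVA comparison as descriptive.

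**The concern.** A one-way ANOVA is valid when group membership was not determined by the variable being tested. Cluster analysis breaks that condition on purpose: it places people in groups so that the input variables are alike within groups and different between them. A small p-value for an input then shows mainly that the algorithm did its job. It does not show that distinct phenotypes exist, or that the variable separates them in the population.

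The Abstract's Discussion paragraph says "A principal study goal is to identify dietary and other personal factors" that distinguish levels of health. If a table of cluster-component p-values were read as evidence on that question, variables could be reported as differentiating factors although no subgroups exist. The article's closing Discussion expects key factors to become covariates in future studies, so such an error could be carried forward.

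**Working it through.** **1. Sample size used for the check.** The Sample size calculations section gives "we need to detect a correlation coefficient (R) = 0.18" and "Establishing 95% power and α = 0.05 level of significance, the target sample size is 22 in each of the 18 categories". The Fisher z formula for a correlation is n = ((z(1−α/2) + z(power)) / atanh(r))² + 3.

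- Two-sided α = 0.05, power 95%, r = 0.18: ((1.960 + 1.645) / 0.1820)² + 3 = 395.4, rounded up to 396 = 22 × 18. This reproduces the plan's figure.
- One-sided α gives 330, which does not reproduce it.
- The plan also says "we aim to enroll an additional 10% of the calculated sample size to account for attrition": 396 × 1.10 = 435.6, in line with 4 × 109 = 436 from the yearly enrolment target.

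The stated sample size is not in dispute. It only fixes n = 396 for what follows.

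**2. Noise simulation.** Each run draws n = 396 people with independent N(0,1) variables, so no clusters exist. The variables are clustered by k-means (best of 3 starts) or Ward's method. Each clustering variable is then tested across the clusters by one-way ANOVA at 0.05. The article gives neither the number of inputs, the number of clusters nor the algorithm, so these are assumptions shown as a range. There were 200 runs per k-means setting and 100 per Ward setting.

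Share of component variables with p < 0.05 (nominal 5%):

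| Inputs | k-means, 2 / 3 / 4 clusters | Ward, 2 / 3 / 4 clusters |
|---|---|---|
| 5 | 85% / 97% / 100% | 82% / 97% / 99% |
| 10 | 78% / 94% / 99% | 72% / 90% / 97% |
| 20 | 68% / 85% / 94% | 57% / 78% / 90% |
| 50 | 54% / 70% / 80% | 41% / 58% / 69% |

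In every run of every setting at least one component variable was below 0.05, and at least one was also below 0.05 divided by the number of inputs. A multiplicity correction therefore does not help.

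**3. Variables outside the clustering.** Fresh noise variables tested across the same clusters were rejected in 3.5% to 6.4% of cases over the settings in the table. A separate set of 1000 runs (10 inputs, 3 clusters, k-means, inputs not rescaled) gave 5.1% for outside variables against 91% for component variables. The median smallest component p-value in those runs was about 3 × 10⁻³⁵.

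**4. Sample splitting.** In the same 1000 runs, one half of the sample was clustered and the other half assigned to the nearest centroid on the same variables. ANOVA in the second half still rejected 80% of component variables. The assignment again uses the variable under test, so the split does not cure the problem.

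**5. Correlated inputs.** With all pairwise correlations 0.3 in one continuous population without subgroups (k-means; 10 inputs with 3 clusters, 50 inputs with 2 or 3), essentially 100% of component variables reached p < 0.05. The lower rates at 50 inputs therefore depend on the independence assumption.

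**The case against.** The strongest reply is that the ANOVA may be meant only to show which variables separate the clusters. The article does not say its p-values will be used to prove that phenotypes exist, and it defers detailed plans. This reduces the likely harm but does not make the test valid. The step is stated here, so a later plan would have to withdraw it rather than merely add detail.

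Four stronger readings are tempting, and the document does not support them.

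- *The main aims fail.* The primary hypotheses concern associations of diet quality and other factors with challenge responses, and the sample size rests on a correlation. Neither depends on this ANOVA. The planned tests of demographic and general characteristics are also sound if those variables stay out of the clustering.
- *Any finding that diet differentiates phenotypes is circular.* That holds only if diet variables enter the clustering in question, and the inputs to the overall clusters are not stated. Dietary intake and physical activity form their own area, and phenotypes are compared between areas, so a comparison of separately built groups is already planned.
- *The chi-square test against standard phenotypes has the same fault.* Standard phenotypes come from literature definitions, not from these data. Where they share inputs with the clusters, the two are truly dependent. Rejecting independence is then correct but uninformative. Sampling bins raise the question only if age, sex or BMI were clustered.
- *Nearly every input will come out significant.* With many independent inputs and few clusters this is too strong, as the last row of the table shows.

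**Conclusion.** The point holds for the component-variable ANOVA. As written, the comparison yields p-values that do not control the type I error. In noise with n = 396, about 41% to 100% of component variables fall below 0.05 for 5 to 50 independent inputs and 2 to 4 clusters, against about 5% for variables outside the clustering.

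The conclusion rests on reading component variables as the clustering inputs. The sentence's position and the separate provision for general characteristics both support that reading. If the term means something else, the article should say so. The size rests on assumed input numbers, cluster numbers and algorithms; the direction was the same in every setting tried. The fault is confined to this step and to any conclusion drawn from its p-values.

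**What to change.** Replace the sentence with:

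> *Component variables will be described by cluster (means, SDs, standardised differences) without p-values; inference on differences between clusters will be made only on variables not used to form them.*

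Three consequences should be stated with it.

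- A dietary or personal factor that is to be tested as differentiating a set of phenotypes should be left out of the inputs to that clustering.
- Clustering half the sample and assigning the other half from the same variables should not be offered as a remedy.
- Where clusters and standard phenotypes share inputs, some association is expected by construction, so the chi-square p-value should not be read as validation of the clusters.

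For the component tables this is a change of wording, and the price is fewer p-values. Leaving a factor out of a clustering does change what that clustering describes, so the choice of inputs should be fixed before the phenotypes are derived. The sample size and data collection need no change.

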## Discussion

This study will provide insights into metabolic variability among healthy US adults that will help guide further research, including controlled intervention trials with foods or whole diets. Many aspects of immune function, metabolomics, physiology, neuroendocrinology, and lifestyle are being investigated in order to identify key factors that may differentiate metabolic health among individuals and thus be important covariates in future studies. The strengths of this study include the multiple dietary data collection tools used for assessment of dietary intake, the broad range of outcomes to be included in the phenotypic analysis, and a study design that minimizes losses to follow-up. The similarity of the challenge meal formula to one previously designed by European Nutrigenomics Organization [18] also provides the potential for comparison with phenotypic flexibility data in a US population to similar data collected in European populations. Limitations of this study include a lack of control group for comparison of the postprandial changes in response to the challenge meal and the unknown contamination of particular measurements that may result from performing other study tasks during the same day (e.g. effects of responding to a questionnaire about food choices on subjective feelings of appetite and hunger). With our study team’s broad range of expertise, we believe that the immense amount of biological data being collected during this study will reveal important differences in metabolic health and phenotypic flexibility.

## Abbreviations

BMI: Body mass index
REDCap: Research electronic data capture
VCO_2_: Volume carbon dioxide produced
VO_2_: Volume oxygen consumed
